### Sample size

The sample size has not yet been calculated using a power analysis due to feasibility and a limited research budget [29]. However, a rationale for numbers in the pilot trial should be included for pilot studies [30]. Based on our previous RCT, we estimate the participation rate would be approximately 2.4% [17]. In this pilot study, we will focus on a prefecture in the Kanto region in Japan, which has approximately 600 PHNs and 1,930,000 residents. Therefore, we will estimate that 14 PHNs were necessary for this study. Owing to ethical considerations, we do not over-recruit the participants. Further, we expect the participant pool to be limited due to the COVID-19 pandemic, which has resulted in a general shortage of PHNs because most will be involved in frontline activities [28].

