### Sampling, informed consent, and randomization

The research team will send 36 invitations to participate (i.e., one to the prefectural government and 35 to the municipal governments) to public health nursing directors in May 2021 and a reminder letter in early June 2021. These directors will be asked to share information about this study with their PHNs. Those who will express interest in participation will be given access to our study website, which will contain a study explanation sheet and written web-based informed consent forms for completion. Only those who will agree to these conditions and will meet the eligibility criteria (as determined by the researchers) will be allowed to participate. The registration period will be from May until the end of June 2021. To ensure privacy, the participants will be registered using pseudonyms and their e-mail addresses.

Figure 1 illustrates a flowchart for the Consolidated Standards of Reporting Trial (CONSORT) design, which will be used throughout the study process. Randomization will be conducted by a researcher specializing in statistics and the co-author via an equal computer-based randomization table. A permuted-block method will be adopted to ensure that the participants will be equally divided between the intervention and control groups. In total, six blocks will be used with four sizes. We will send an e-mail to all participants informing them of their assigned group.

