### Statistical analysis

We will conduct descriptive statistics (e.g., recruitment rate, dropout rate, and data completion rate) to assess the feasibility of this study and analyze intergroup baseline differences in the data and primary outcomes using the Mann-Whitney *U*-test and the chi-square/Fisher exact test. We will assess whether previous experience in local healthcare planning and other factors affected the study outcomes based on the results of the Mann-Whitney *U*-test and the chi-square/Fisher exact test. Analyses will be performed according to the intention-to-treat principle. We will use IBM SPSS for Windows (version 25; IBM Corp, Armonk, NY, USA) for the analysis and *p*-values < .05 indicating statistically significant intergroup differences. This study is expected to have a power ≥.80 and α ≤.05, assuming a medium effect size (*d* = .30) [35].

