As mentioned, participants in the control group can access the same learning program in the post-intervention context, providing them with critical education while minimizing the number of dropouts and ensuring educational equality. Further, we will assess whether previous experience with local healthcare planning impacts the study outcomes. These results will be used to revise different aspects of the program and the inclusion criteria for a future definitive RCT.

We have also identified some potential limitations. First, the pilot study only included a small sample from one prefecture in Japan. In this regard, the participants will be likely to have strong interests in the nature of the study program, thus increasing their motivation to engage in continued education. This may result in selection bias and influence the distribution of data. However, this study will focus on the feasibility of the program, not its effectiveness. Regardless, these issues should be carefully considered when interpreting the data.

Second, we will protect the privacy of all participants by anonymizing the data and did not collect the names of the local governments where they are employed. As such, we cannot rule out the possibility that eligible participants from the same local governments will be allocated to different study groups. In this regard, we cannot entirely prevent contamination or instances in which the program content is leaked from the intervention group to the wait-listed control group. We will explain this issue to all participants and repeatedly ask the intervention group to keep the program contents confidential.

Third, we could not control some confounding factors, such as the provenance area of participants and rural versus urban areas and the lack of follow-up assessment in this study. Fourth, only five PHNs confirmed the web-based self-learning modules due to the COVID-19 pandemic. Fifth, the reliability and validity of the Japanese version of Fisher’s Self-Directed Learning Readiness Scale has not been confirmed. Thus, we could not use this scale in this study.

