Despite these limitations, this pilot RCT will assess the feasibility of a newly developed web-based self-learning program designed to increase the involvement of PHNs in local healthcare planning while also providing the preliminary data needed for a future definitive RCT in Japan. Therefore, we will confirm whether the web-based, self-learning system is considered user-friendly and whether participants exhibit improved competencies in the local healthcare planning context following the intervention.

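### The stated power of at least .80 at d = .30 contradicts the planned 14 participants, for whom it is about 6% to 8% (two-sided)

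*Protocol article*

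**What the plan says.** The protocol article makes two statements that bear on power.

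- **Statistical analysis:** "This study is expected to have a power ≥.80 and α ≤.05, assuming a medium effect size". The effect size is given as d = .30. The same section plans Mann-Whitney and chi-square or Fisher tests, with p-values "< .05 indicating statistically significant intergroup differences". It does not say whether tests are one- or two-sided.
- **Sample size:** "The sample size has not yet been calculated using a power analysis due to feasibility and a limited research budget". The number comes from an expected participation rate of 2.4% among about 600 nurses: "we will estimate that 14 PHNs were necessary for this study". Over-recruitment is ruled out on ethical grounds. Allocation is 1:1 (Trial design and settings), so 7 per arm.

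The Discussion says that "this study will focus on the feasibility of the program, not its effectiveness". It also says the authors will confirm "whether participants exhibit improved competencies in the local healthcare planning context following the intervention".

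**The concern.** The power sentence is about this study, not the later definitive trial. It credits a 14-person pilot with a power that normally takes several hundred participants at an effect of this size, and it stands in the same article as the statement that no power analysis was done.

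At stake is how the between-group result is read. Someone told that power is at least .80 will take p above .05 as evidence against an effect of d = .30. If the power is really below 10%, that result is expected more than nine times in ten even when the effect is real. Conversely, with low power and a small true effect, the results that reach significance are the exaggerated ones. This matters here because the Background and the Discussion plan to use the pilot data to calculate the sample size of the definitive trial.

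**Working it through.** **Inputs from the protocol article:** d = .30, α = .05, stated power ≥ .80 (Statistical analysis); N = 14, that is 600 × 0.024 = 14.4 (Sample size); 1:1 allocation, so n = 7 per arm (Trial design and settings). Because d is standardised, no SD is needed.

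**Assumptions:** two-sided test unless noted, all 14 analysed, normal data.

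**1. Trying to reproduce the stated power.** Noncentrality for two equal arms is d × √(n/2) = 0.30 × √3.5 = 0.561. The normal approximation gives Φ(0.561 − 1.960) = Φ(−1.399) = 0.081. The exact t-test calculation (noncentral t, 12 degrees of freedom) also gives 8.1%. The planned test is Mann-Whitney; its exact two-sided version, simulated with normal data, gives 6.1% to 6.4% depending on the run. The stated .80 is not reproduced.

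**2. Size needed for .80.** n per arm = 2 × (1.960 + 0.842)² / 0.30² = 174.4, so 175 by the normal approximation. The t-test needs 175.4, so 176 per arm, or 352 in all. That is 352/14 ≈ 25 times the planned number and 352/600 ≈ 59% of the nurses in the prefecture, against an expected 2.4%. Mann-Whitney, at relative efficiency 0.955, needs 175.4/0.955 = 183.7, so 184 per arm.

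**3. Smallest detectable effect.** Solving the t-test power for d at n = 7, two-sided .05 and 80% power gives d = 1.63.

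**4. More generous readings** (t-test):

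| Reading | Power |
|---|---|
| One-sided, 7 per arm | 13% |
| Two-sided, 12 per arm | 11% |
| Baseline-adjusted, assumed correlation 0.5 / 0.7 / 0.9, 7 per arm | 9% / 11% / 22% |
| d = .50 instead of .30, two-sided, 7 per arm | 14% |
| Pre-post in all 14, d = .30 for the change, two-sided / one-sided | 18% / 28% |

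The highest figure at N = 14 is 28%. It belongs to a before-after comparison, not to the between-group test that the section describes.

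**5. A less generous reading.** The feasibility section gives a 50% figure for dropout and data completion in unclear wording. If half the data were lost, leaving 3 to 4 per arm, two-sided power would be 6.0% to 6.5% by t-test, and about 3.6% by exact Mann-Whitney at 4 per arm.

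**6. What a p-value would then mean.** With a true d of .30 and 7 per arm, simulated results with exact Mann-Whitney p below .05 had a mean absolute difference of about 1.24 SD, roughly four times the truth. About 7% to 8% of them pointed the wrong way. With an SD of 1, the half-width of a 95% interval is about 2.179 × √(2/7) = 1.16 SD, so the estimate would be compatible with a wide range of effects.

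**The case against.** The strongest reply is that this is a pilot and the article largely says so. It states that no power analysis was done, calls the effects preliminary, names the small sample as a limitation and puts its focus on feasibility. The power sentence did not set the sample size, so no design element rests on it. This stands as mitigation, and nothing here asks for a larger pilot. It does not make the sentence true, and the fault is not an omission that a fuller document could supply.

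A reader might infer more than the documents support:

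- **That the trial can support no conclusion at all.** An effect near d = 1.63 would be detectable, and the recruitment, dropout and completion rates are descriptive and do not depend on power.
- **That the article gives several conflicting sample sizes.** It states one, 14. The figure of 352 is calculated here. The randomization section says "In total, six blocks will be used with four sizes", which on one reading makes 24 places. That sentence is unclear, and a block list longer than expected recruitment is not a target size.
- **That p below .05 is the success criterion.** No section says so. The stated success criteria are feasibility rates. The threshold only labels intergroup differences, and the plan to look at improved competencies sets no significance rule.
- **That the competency scale must therefore stop being the primary outcome.** That would change the outcome hierarchy of a registered trial whose recruitment is complete. It is a separate and debatable question and does not follow from a wrong power figure.

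It is also fair to say that 6% to 8% rests on two-sided testing and full retention, neither of which the article fixes. The alternatives above move the figure but do not bring it near .80.

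**Conclusion.** Wrong as written. At d = .30 and the planned 14 participants, power is about 8% (two-sided t-test) or 6% (two-sided exact Mann-Whitney), against a stated value of at least .80: roughly a tenfold overstatement. These figures assume 7 per arm, full retention and normal data. A one-sided t-test gives about 13%, and no variant tried at this N exceeds 28%. The sentence also contradicts the article's own account of how the size was chosen.

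The consequence is limited to the between-group outcome tests. A non-significant p-value there is uninformative about d = .30. A significant one would overstate the effect if the truth is near .30; that would not follow if the true effect were very large.

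**What to change.** - Delete the power sentence, or assign it explicitly to the future definitive trial.
- In its place, state that 14 participants are not powered for efficacy, and give the figure with its assumptions: about 6% to 8% at d = .30, two-sided α = .05, 7 per arm, full retention.
- Report between-arm outcome differences with 95% confidence intervals as preliminary estimates, and do not use p below .05 as evidence for or against effectiveness.

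The sample size, the feasibility criteria and the outcome hierarchy stay as they are. The cost is a change of wording and of emphasis in reporting, and a stated figure becomes less favourable.

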### A content analysis

We will conduct a content analysis using all participant feedback provided through the free descriptions mentioned earlier, specifically regarding their feasibility and the web-based self-learning program itself. This will be done by entering relevant information into a Microsoft Excel worksheet. We will code all data and sort the results based on their commonalities. The positive comments will help assess the feasibility of this study, and the negative comments will contribute to improving the program.

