### Assessment of the trial feasibility

We will assess the feasibility of this study based on the recruitment rate, dropout rate, and data completion rate. We will set the corresponding criteria to assess the success of feasibility; the recruitment rate will be 2.4%, the dropout rate, and the data completion rate will be 50% based on the previous pilot study [12]. We also will ask the participants for their feedback on the feasibility of the trial and web-based learning self-learning program, clarifying areas that need improvement and/or continual refinement as open-ended survey questions.

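### As worded, the content analysis gives only positive comments a role in judging feasibility, so the open-ended feedback can count for feasibility but not against it

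*Protocol article*

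**What the plan says.** The protocol article describes two kinds of evidence on feasibility.

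- **Quantitative.** Under Assessment of the trial feasibility: "We will assess the feasibility of this study based on the recruitment rate, dropout rate, and data completion rate". Criteria are set in advance: "the recruitment rate will be 2.4%, the dropout rate, and the data completion rate will be 50% based on the previous pilot study". The Statistical analysis section repeats this basis: "We will conduct descriptive statistics (e.g., recruitment rate, dropout rate, and data completion rate) to assess the feasibility of this study".
- **Qualitative.** The same feasibility section adds open-ended survey questions: "We also will ask the participants for their feedback on the feasibility of the trial and web-based learning self-learning program, clarifying areas that need improvement".

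The section A content analysis then explains how the answers are handled. The input is unrestricted: "We will conduct a content analysis using all participant feedback provided through the free descriptions mentioned earlier". So is the coding: "We will code all data and sort the results based on their commonalities". The section closes by saying what each class of comment is for: "The positive comments will help assess the feasibility of this study, and the negative comments will contribute to improving the program".

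**The concern.** The closing sentence names two uses and assigns evidence to each by whether it is favourable. A remark that a nurse had no time for the modules, could not log in or found the content irrelevant is direct evidence about feasibility. Under this sentence it goes to program revision, and nothing says that it also enters the feasibility assessment.

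Two features of the trial give this weight.

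- Feasibility is the declared purpose. The Discussion says that the study is about feasibility and not effectiveness, and it expects volunteers who are already keen on the subject. In a sample of about 14, a few unfavourable comments may be among the most informative evidence available.
- The three rates describe how the trial ran. None of them asks whether the modules were usable, relevant or manageable at work. The Discussion also promises to establish whether participants find the system user-friendly, and the open-ended questions are the only listed measure that asks them.

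**Working it through.** The plan states no figure on this point, so there is none to reproduce. The check is a comparison of sections, followed by an illustration.

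**Step 1: what the feedback is meant to cover.** The Abstract and Assessment of the trial feasibility both say that comments are sought on the trial as well as on the program, with the aim of finding what needs improvement. Unfavourable comments on the trial are therefore expected input.

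**Step 2: where each type of comment goes under the closing sentence of A content analysis.**

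| Comment | Stated use |
|---|---|
| Positive, on program or trial | Feasibility assessment |
| Negative, on the program | Program improvement |
| Negative, on the trial (registration, website, surveys) | Program improvement, although the comment is not about the program |

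The third row is where the text fits worst with step 1. Such a comment bears on trial feasibility and on the design of the definitive trial, and the sentence names neither as its use.

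**Step 3: whether another section supplies the missing route.** Statistical analysis mentions only the descriptive rates for feasibility. The Discussion and Conclusions speak of feedback and revision in general terms. No section gives negative comments a role in the feasibility judgement.

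**Step 4: illustration.** Let P be the number of positive comments and N the number of negative comments.

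- All comments used: positive share = P / (P + N).
- Split read literally: positive share = P / P = 100% whenever P is at least 1.

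| Assumed true positive share | All comments used | Split as worded |
|---|---|---|
| 10% | 10% | 100% |
| 50% | 50% | 100% |
| 90% | 90% | 100% |

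The shares are assumptions, not figures from the protocol. For scale, suppose that each of the 14 planned participants gives one comment, independently, with a 10% chance that it is positive. The chance of at least one positive comment is 1 − 0.9^14 = 0.771. Even strongly unfavourable feedback would then usually leave something to report in favour of feasibility.

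**The case against.** The strongest reply is that this is one loose sentence in a condensed article. It says that positive comments help with the assessment. It does not say that they alone count, and it does not say that negative ones are set aside. All feedback is analysed and coded, and the request in Assessment of the trial feasibility, "We also will ask the participants for their feedback on the feasibility of the trial and web-based learning self-learning program", is neutral as to direction. The sentence could be naming the main use of each type of comment.

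Part of this stands: the exclusion of negative comments is the natural reading, not an explicit prohibition. But coding everything does not undo a selection made when the codes are put to use. The word help acknowledges that other evidence also counts, which fits the three rates, and it gives unfavourable comments no role.

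A reader might also infer more than the documents support:

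- **That feasibility as a whole will be judged from favourable comments only.** It will not. The three rates come first, have preset criteria and can fail whatever anyone writes. Severe barriers would be expected to show in dropout and completion.
- **That a go decision for the definitive trial would rest on the filtered comments.** No section defines a qualitative verdict, a threshold or a go/no-go rule based on comments.
- **That up to half the sample may drop out and go unheard.** The 50% figure is a feasibility criterion, neither a forecast nor a ceiling. Dropout itself already counts as a feasibility measure. That those who leave give no feedback is a plausible inference from survey-based collection, but it is not stated. How reasons for leaving are collected is detail that an article may leave to the full protocol.

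**Conclusion.** The point holds for the qualitative component only. As worded, the open-ended feedback can favour feasibility but cannot count against it, and negative comments on trial procedures have no stated route into the judgement. The direction of the bias is clear. Its size is not estimable, because it depends on how many unfavourable comments are made and on how much weight the comments carry beside the rates, and the documents give neither.

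The conclusion rests on reading the closing sentence of A content analysis as an assignment of use, and on the absence of any other section that gives negative comments a part in assessing feasibility. The quantitative assessment is unaffected, so this is a minor to moderate weakness. It is still worth correcting, because it touches the study's main aim and the remedy is very cheap.

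**What to change.** Reword the closing sentence of A content analysis to say that positive and negative comments, coded as facilitators and barriers, both inform the feasibility assessment and both inform refinement of the program and of the trial procedures. State that the number of participants raising each theme will be reported.

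Counts over all participants are enough. The article does not say when the wait-list group gives its feedback. If it does so at the September post-test, it will not yet have used the modules, which it receives in October to November, and counts of program themes would not be comparable between groups.

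The cost is one sentence and a simple tally, with no new data collection. The only downside is that the feasibility statement may become slightly less favourable.

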## Discussion

This pilot RCT will aim to confirm the feasibility and preliminary effects of a web-based self-learning program designed to increase the involvement of PHNs in local healthcare planning by enhancing relevant competencies. We will also examine the eligibility of the implemented outcome scales and data collection procedures in preparation for a future definitive RCT. The strengths of the novel self-learning program are as follows: (1) user-friendly web-based educational program, (2) eligible participants will be selected based on clear criteria, (3) all participants will be given equal opportunities to learn about local healthcare planning through the program (i.e., after we collect data from the intervention group), and (4) primary outcomes will be measured using validated standardized scales. This study also has the strength that PHNs will understand theoretical concepts and practical strategies relevant to healthcare planning without contact with other participants due to the COVID-19 pandemic.

We developed the abovementioned program based on several components, including adult learning theory [31], a nationwide survey [25], and previous related studies [5, 16, 17, 21, 23, 25]. Through participation in web-based self-learning modules, the participants can acquire the competencies of local healthcare planning and bridge the gaps between the community health needs that PHNs must address in daily practice and the context of newly developed local healthcare plans. The development of local healthcare planning can improve health inequities by bridging the gaps in community health needs [6]. In this regard, PHNs are responsible for enhancing health equity and developing needs-oriented health policy through their practices [4, 5]. This pilot feasibility study will also adopt validated outcome scales, which will be used to gather the preliminary data needed to calculate an appropriate sample size for a future large-scale RCT. Owing to the constraints of the COVID-19 pandemic, we will also ensure that participants are socially distanced to prevent infection. More specifically, our web-based learning modules do not require participants to make direct contact with one another and will also eliminate travel time.

As mentioned, participants in the control group can access the same learning program in the post-intervention context, providing them with critical education while minimizing the number of dropouts and ensuring educational equality. Further, we will assess whether previous experience with local healthcare planning impacts the study outcomes. These results will be used to revise different aspects of the program and the inclusion criteria for a future definitive RCT.

We have also identified some potential limitations. First, the pilot study only included a small sample from one prefecture in Japan. In this regard, the participants will be likely to have strong interests in the nature of the study program, thus increasing their motivation to engage in continued education. This may result in selection bias and influence the distribution of data. However, this study will focus on the feasibility of the program, not its effectiveness. Regardless, these issues should be carefully considered when interpreting the data.

Second, we will protect the privacy of all participants by anonymizing the data and did not collect the names of the local governments where they are employed. As such, we cannot rule out the possibility that eligible participants from the same local governments will be allocated to different study groups. In this regard, we cannot entirely prevent contamination or instances in which the program content is leaked from the intervention group to the wait-listed control group. We will explain this issue to all participants and repeatedly ask the intervention group to keep the program contents confidential.

Third, we could not control some confounding factors, such as the provenance area of participants and rural versus urban areas and the lack of follow-up assessment in this study. Fourth, only five PHNs confirmed the web-based self-learning modules due to the COVID-19 pandemic. Fifth, the reliability and validity of the Japanese version of Fisher’s Self-Directed Learning Readiness Scale has not been confirmed. Thus, we could not use this scale in this study.

Despite these limitations, this pilot RCT will assess the feasibility of a newly developed web-based self-learning program designed to increase the involvement of PHNs in local healthcare planning while also providing the preliminary data needed for a future definitive RCT in Japan. Therefore, we will confirm whether the web-based, self-learning system is considered user-friendly and whether participants exhibit improved competencies in the local healthcare planning context following the intervention.

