## Methods

### Trial design and settings

A pilot prospective RCT design will be implemented among single-blind participants and parallel groups. To ensure equal learning opportunities for both groups, PHNs who will answer a pre-test survey and register for this study will be randomly allocated to the intervention or wait-listed control groups [1:1]; as such, a double-blind design was not possible. All PHNs will be exposed to the same self-learning program; the intervention group will participate in the program first, and then, the wait-listed control group will be offered the same program. All participants will answer a post-test survey.

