### Outcomes and data collection

Using the study website, the eligible participants will provide demographic data and will complete the outcome scales at the baseline and post-intervention. More specifically, demographic data will include gender, age, years of PHN experience, job title, educational background, affiliation, previous experience with local healthcare planning education at the undergraduate level and on-the-job training after graduation, previous experience with local healthcare planning, whether they worked with colleagues who played active roles in healthcare planning, and information on promoting the daily practices of PHNs. To decrease the number of dropouts, we will send e-mails to all participants with information about the study progress and will remind them to answer the post-test questions. At the baseline and post-intervention, the participants will address the following outcomes.

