#### Competencies related to involvement in health policy

The primary outcome will be measured using a self-reported 16-item scale targeting PHN competencies in public health policy in the context of Japanese local governments [33]. The scale was confirmed as reliable and valid for use in Japan and is only available in Japanese. The first eight items measure community partnership among PHNs when developing health policy, while the remaining items evaluate competencies related to the community nursing diagnosis cycle. All items will be measured using a 4-point Likert scale, ranging from 0 to 3: 0 (unable to do), 1 (partially unable to do), 2 (partially able to do), and 3 (able to do).

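### The tests of previous experience contain no arm-by-factor contrast, so they cannot show whether the program's effect differs between nurses, yet their result is to inform the definitive trial's inclusion criteria

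*Protocol article*

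**What the plan says.** The Statistical analysis section of the protocol article gives the method: "We will assess whether previous experience in local healthcare planning and other factors affected the study outcomes based on the results of the Mann-Whitney" test and the chi-square/Fisher exact test. The only significance threshold in that section is p < .05.

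The Discussion repeats the aim for one factor, previous experience ("Further, we will assess whether previous experience with local healthcare planning impacts the study outcomes"), and then gives its use: "These results will be used to revise different aspects of the program and the inclusion criteria for a future definitive RCT".

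The primary outcome is a "self-reported 16-item scale targeting PHN competencies in public health policy", with each item scored 0 to 3. Participants "will complete the outcome scales at the baseline and post-intervention". The section describing the intervention places the post-test in September 2021 and the control group's access in October to November. The abstract gives the same order. Only the intervention arm has therefore used the modules when the compared outcomes are measured.

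No section plans a comparison of the arms within levels of experience, or any other arm-by-factor contrast.

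**The concern.** If the aim is to decide for whom the program is suitable, the quantity needed is the program's effect in nurses with more and with less experience. A rank test of outcomes between kinds of nurse has a different null: that the scores have the same distribution in both groups. On a self-rated competency scale, nurses with more experience may rate themselves higher before opening any module. If the test uses post-test scores, it can then reject although everyone gains the same amount. In the other direction, a comparison that ignores arm mixes exposed and unexposed nurses and so dilutes a real difference in response.

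At stake is one of the pilot's stated products. Eligibility for the definitive trial could be changed because of who scores high, not because of who benefits.

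**Working it through.** **Inputs from the protocol.** Sample size: 600 nurses × 2.4% = 14.4, which reproduces the stated 14. Allocation is 1:1, so 7 per arm. The test is Mann-Whitney at p < .05. The control arm is unexposed at the post-test.

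**Assumptions (not in the protocol).** The factor has two levels, split 7/7 and nearly balanced over the arms (4+3 and 3+4). The first set has a baseline-to-post correlation of 0.6 and a common program effect of 0 or 0.5 SD (40,000 runs per setting). The second set has a correlation of 0.7, a common effect of 0.3 SD and random placement of the factor over the arms (3,000 runs per setting).

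**Step 1: what each contrast estimates.** Let L be the entry difference between levels and D the extra program effect at the higher level. With about half of each level in the intervention arm, the expected values are:
- difference between levels in post-test score, arms pooled: L + D/2
- difference between levels in change, arms pooled: D/2
- between-arm difference in change at the higher level, minus the same at the lower level: D

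Only the last is the difference in program effect.

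**Step 2: equal benefit for all (D = 0), 14 nurses.** Probability that the factor is declared significant:

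| L (SD) | Post-test, set 1 | Post-test, set 2 | Change, set 1 | Change, set 2 | Arm-by-factor test, set 2 |
|---|---|---|---|---|---|
| 0 | 3.3-3.7% | 4.1% | 3.2-3.9% | 3.9% | 5.2% |
| 0.5 | 11.1-12.0% | 11.5% | 3.2-3.9% | 3.5% | 4.4% |
| 1.0 | 34.2-35.6% | 33.5% | 3.2-3.9% | 3.9% | 4.4% |
| 1.5 | 65.8-66.9% | 65.4% | 3.2-3.9% | 3.5% | 5.1% |

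The exact test's true size at 7 against 7 is 3.8%, so the change-score rates show no false flagging beyond chance. A larger sample makes the post-test version worse: with 100 nurses it flags 67%, 99.7% and 100% at L = 0.5, 1.0 and 1.5.

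**Step 3: a real difference in effect (L = 0, D = 1 SD), arms pooled.** The expected contrast is 0 + 1/2 = 0.5 SD. Detection is about 9-12% over post-test and change scores.

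**Step 4: a masked difference (L = -0.5, D = 1 SD).** The post-test contrast is -0.5 + 1/2 = 0. The post-test comparison flags 3%, although the program helps only one kind of nurse.

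**Step 5: the intervention arm alone.** With 7 nurses split 3 against 4, the smallest two-sided exact p-value is 2/35 = 0.057, so the exact test can never reach .05. With 100 nurses, the post-test version in this arm still flags 38% to 100% at L = 0.5 to 1.5 when benefit is equal.

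**Step 6: a formal interaction test is no cure at this size.** With 14 nurses its power is 9% for D = 0.6 SD and 14% for D = 1 SD.

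**The case against.** The strongest objection is that the method is only partly stated. The protocol does not say whether the factor check uses post-test scores or change, or whether the arms are pooled. Both time points are collected, and an article may leave such detail to a fuller document. A reader might infer that raw post-test scores with pooled arms are the fixed plan, and that false flags of up to two-thirds will therefore occur. The documents do not support that. The false-flag rates hold only for post-test scores and assumed entry differences, and on change scores they vanish. What remains on any reading is that no arm-by-factor contrast is planned.

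Several further limits stand:
- A reader might infer that all the factors feed the inclusion criteria. The Discussion ties only previous experience to them; the "other factors affected the study outcomes based on the results of the Mann-Whitney" wording in the Statistical analysis section is not linked to eligibility.
- The eligibility criteria already require planning experience, so this factor can vary only in amount or type. Entry gaps of 1 to 1.5 SD are less certain for it.
- Program revision also draws on the content analysis of participants' comments, so these tests are not its only source.
- Score level can legitimately bear on eligibility, for instance through headroom on items capped at 3. It would be too strong to say that only a difference in program effect may be used.
- With 14 nurses no analysis will be precise, and the Discussion says that the focus is feasibility and urges care in interpretation.

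The last point argues against a significance rule here. It does not justify choosing a contrast that answers a different question, because the same Discussion commits the result to a decision about the next trial.

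**Conclusion.** The point holds in a limited form. Two-group tests of outcomes by experience show who scores differently. They do not show whether the program's effect differs, and nothing else in the protocol does.

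The size depends on a choice that the protocol leaves open. On post-test scores, equal benefit is mistaken for an influence of the factor in about 11-12%, 34-36% and 66-67% of trials, for assumed entry differences of 0.5, 1 and 1.5 SD with a 7/7 split. On change scores the rate is 3-4%, and the remaining weakness is that pooling the arms roughly halves a true difference in effect (about 9-12% detection of a 1 SD difference).

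This does not affect the feasibility assessment. It affects what can be carried forward to the definitive trial's inclusion criteria.

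**What to change.** In the Statistical analysis section and the Discussion, replace the significance tests of outcomes by factor with a descriptive table. It should show change from baseline by level of experience, separately by arm, with the between-arm difference in change at each level and its 95% CI, and no p-value rule. Define the levels as amount or type of planning experience, since every participant must have some.

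Add two statements. First, a difference in score level alone is not evidence that the program works better or worse in those nurses. Second, any use of these results for the inclusion criteria is hypothesis-generating.

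The cost is some wording and one table from data already collected. The downside is precision, because each cell holds 3-4 nurses. With the assumed correlation of 0.6, the SD of change is √(2 × (1 − 0.6)) = 0.89 SD. For 3 against 4 nurses the standard error is 0.89 × √(1/3 + 1/4) = 0.68 SD. The 95% half-width is 2.571 (t, 5 df) × 0.68 ≈ 1.8 SD. Intervals this wide make it plain that the pilot cannot settle who benefits.
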